### 4.3 Exclusion criteria

A potential subject who meets any of the following criteria will be excluded from participation in this study:

- Pregnant or breast-feeding females
- Evidence of clinically significant neurologic, cardiac, pulmonary, hepatic, hematologic, rheumatologic, endocrine, autoimmune, oncologic, or renal disease
- Any laboratory test which is abnormal, and which is deemed by the Investigator(s) to be clinically significant
- Behavioral or cognitive impairment or psychiatric disease that in the opinion of the investigator affects the ability of the subject to understand and cooperate with the study protocol
- Current alcohol/illicit drug/nicotine abuse or addiction: history or evidence of current drug use or addiction (positive drug screen for amphetamines, barbiturates, benzodiazepines, cannabinoids, cocaine, or opiates) or signs of excessive use of alcohol at screening and at day 0.
- Presence of any febrile illness ( $T \geq 38.0^{\circ}\text{C}$  or lab confirmed viral disease (PCR)) or symptoms suggestive of a viral respiratory infection within 1 weeks prior to vaccination. Participants will be screened for SARS-Cov-2 with an EUA-approved PCR test at screening, and at day 0.
- Use of corticosteroids (excluding topical preparations for cutaneous or nasal use) or use of immunosuppressive drugs within 30 days before inoculation
- A history of anaphylaxis, history of allergic reaction to vaccine, known allergy to one of the components in AKS-452X. Mild allergies without angio-edema or treatment need can be included if deemed not to be of clinical significance (including but not limited to allergy to animals or mild seasonal hay fever)
- A history of asthma within the past 10 years, or a current diagnosis of asthma or reactive airway disease associated with exercise
- Receipt of blood or blood-derived products (including immunoglobulin) within 6 months prior to vaccination.
- Receipt of another investigational agent within 30 days or 5 times the product half-life (whichever is longest) prior to vaccination
- Deprived of freedom by an administrative or court order or in an emergency setting
- Any condition that in the opinion of the principal investigator (PI) would jeopardize the safety or rights of a person participating in the trial or would render the person unable to comply with the protocol.

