
#### **1.4. Background use of Naked Booster AKS-452 without Adjuvant Montanide (AKS-452X)**

Phase I of the ACT-study has successfully been closed through the day 56 visit, and during the interim-analysis and evaluation by the DSMB, AKS-452 in all dosing groups showed a very favorable outcome in terms of safety, tolerability and immunogenicity. Based on the safety profile, seroconversion rate per dosing cohort and the statistical re-assessment, it was determined to start the subsequent randomized open-label phase II study with one cohort of 2x45 µg twice injection and 1x90 µg single-injection with each cohort consisting of 26 participants. As it becomes more apparent that the current registered vaccines may require additional boosting, especially in the face of more infectious variants (e.g. the delta mutant), the phase I study was amended with a boosting arm for all the cohorts that received a single-injection (i.e. 22.5 µg, 45 µg, and 90 µg) of the concentrated AKS-452 vaccine (AKS-452X,) which is currently underway. To maximize the benefit of the booster, the aforementioned phase I single-injection groups are receiving a single additional injection of non-adjuvanted AKS-452X at the 90 µg dose level, which was the highest and most effective dose used in the phase I adjuvanted cohorts. In the underlying Study Protocol, we propose the same booster dose for boosting subjects after vaccination with one of the four registered vaccines (i.e. Pfizer [Comirnaty], Moderna [Spikevax], Janssen [Ad26.COV2.S], AstraZeneca [Vaxzevria]). Additional justifications for implementing a 90 µg non-adjuvanted AKS-452X booster are as follows.

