| Route of administration                           | Subcutaneous                                                                                                                                                                                                                                                                                                                                                                                                                                                                                                                                   |
| Product presentation                              | Multi-dose vials; 1.0 mL fill with $\geq 0.8$ mL extractable volume of AKS-452X (concentrated)                                                                                                                                                                                                                                                                                                                                                                                                                                                 |
| Dosage                                            | 
 
• 90 µg of the SP/RBD-Fc antigen.
 
                                                                                                                                                                                                                                                                                                                                                                                                                                                            |
| Booster Dosage schedule                           | 
 
• Maximum of one booster immunization regardless of age <math>\geq 3</math> months after last vaccination dose
 
• Potential booster immunizations no more frequently than every 6 months
 
                                                                                                                                                                                                                                                                                             |

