### 4.2 Inclusion criteria

In order to be eligible to participate in this study, a subject must meet all of the following criteria:

- Age 18-85 years (extremes included), males and females.
- Body mass index (BMI) between 19.0 and 30.0 kg/m^2, inclusive
- General good health, without significant medical illness, as determined via physical exam findings, or vital signs
- No clinically significant laboratory abnormalities as determined by the investigator
  - o Note: one retest of lab tests is allowed within the screening window
- Informed Consent Form signed voluntarily before any study-related procedure is performed, indicating that the subject understands the purpose and procedures required for the study and is willing to participate in the study
- Willing to adhere to the prohibitions and restrictions specified in this protocol
- All participants have received a completed (registered) vaccine at least 3 months before inclusion in this study (i.e. Pfizer [Comirnaty], Moderna [Spikevax], Janssen [Ad26.COV2.S], AstraZeneca [Vaxzevria]).
- Negative hepatitis panel (including hepatitis B surface Ag and anti-hepatitis C virus Abs) and negative human immunodeficiency virus Ab and Ag screens at screening
- Female subjects should fulfil one of the following criteria:
  - o At least 1 year post-menopausal (amenorrhea >12 months)
  - o Surgically sterile (bilateral oophorectomy, hysterectomy, or tubal ligation);
  - o Will use adequate forms of contraceptives from screening to discharge.
- Female subjects of childbearing potential and male subjects who are sexually active with a female partner of childbearing potential must agree to the use of an effective method of birth control from screening to discharge
  - o Note: medically acceptable methods of contraception that may be used by the subject and/or partner include combined oral contraceptive, contraceptive vaginal ring, contraceptive injection, intrauterine device, etonogestrel implant, double barrier, sterilization and vasectomy
- Female subject has a negative pregnancy test at screening and upon check-in at the clinical site.
  - o Note: pregnancy testing will consist of a serum pregnancy test at screening and urine pregnancy tests at the dosing visit, in all women.

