### 5.4 Summary of known and potential risks and benefits

#### *Overall Conclusion for Phase I Data*

The overall safety assessment of AKS-452 in the ongoing phase I/II ACT clinical study in six cohorts totaling 60 participants in phase I and 52 in phase II, showed limited side-effects over all dosing-cohorts. No SAEs attributable to the vaccine were observed. Mild AEs due to the vaccine were observed, comparable to the current registered anti-COVID-19 vaccines. Moreover, no laboratory abnormalities were observed which were attributable to the vaccine. In all dosing cohorts, a  $\geq 70\%$  seroconversion rate was observed, whereas the results for each of the cohorts after a single dose were comparable to values measured from confirmed COVID-19 positive convalescent serum samples. 100% seroconversion was seen in the cohorts using 2x 45 µg, 1x 90 µg and 2x 90 µg.

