### 9.3 Primary study parameter(s)

The primary aim of this booster vaccination study is to investigate if a subcutaneous (s.c.) booster dose of 90 µg of the naked Akston AKS-452X vaccine at  $\geq 3$  months post initial vaccination, with any of the four registered vaccines, will boost the antibody titer and immune response in human healthy volunteers 4weeks after s.c. injection.

Safety: Adverse events are defined as any undesirable experience occurring to a subject during the study, whether or not considered related to the investigational product / trial procedure/ the experimental intervention. All adverse events reported spontaneously by the subject or observed by the investigator or his staff will be recorded.

Evaluation of Safety and Tolerability:

Safety and tolerability will be assessed through AEs and clinical laboratory, and any other parameter that is relevant for safety assessment.

Adverse Events: a listing of all individual AEs will be provided. Summary tables of TEAEs will be presented by system organ class based on the MedDRA terminology list (preferred terms): containing the number of TEAEs (frequency of occurrence, number of subjects experiencing the event) by treatment and containing the number of drug-related TEAEs (frequency of occurrence, number of subjects experiencing the event) per treatment. Additional tables of total counts by treatment and relationship and by treatment and severity will be given.

Laboratory data: clinical laboratory data will be listed accompanied by an indication if the parameter is outside the reference range. A summary of all data outside the reference range of the clinical laboratory will be provided. Clinical laboratory data will be presented descriptively, where applicable.

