The AKS-452 vaccine has been evaluated in a combined phase I/II clinical study (<https://clinicaltrials.gov/show/NCT04681092>). The initial data of the phase I study have been evaluated by the DSMB (see Appendix A). Phase II is currently ongoing and as part of an ongoing combined phase I/II clinical study, expected to be finalized February 2022, last follow-up.

c. Can the primary or secondary mechanism be induced in animals and/or in *ex-vivo* human cell material?

Yes, the vaccine is potent at inducing high titers of neutralizing Abs after single and double low-dose administrations via s.c. routes in mice, rabbits, non-human primates and humans (phase I/II).

d. Selectivity of the mechanism to target tissue in animals and/or human beings

The selectivity has been extensively tested and evaluated in human cells and animals (see IB / IMPD), and in human beings through a phase I/II study.

e. Analysis of potential effect

The vaccine is composed of one main component: the SP/RBD-Fc fusion protein antigen. The SP/RBD-Fc antigen is given at extremely low dose levels because of its design to function locally in the proximity of the injection site. Therefore, this component does not have any associated serious practical risks.

f. Pharmacokinetic considerations

Because such low doses of the vaccine are administered, the vaccine does not achieve any detectable systemic levels.

g. Study population

Healthy volunteers

h. Interaction with other products

Not applicable

i. Predictability of effect

The levels of neutralizing Abs measured in the ACE2-SP/RBD binding ELISA that are as high as those in human convalescent serum are a good predictability marker of efficacy, which is the case with other vaccines already evaluated in Phase III COVID-19 efficacy trials. In addition, the induction of SP/RBD-specific Th1 T cells, measured via IFN- $\gamma$  ELISPOT assay, are confirmation that the vaccine induces the SARS-Cov-2 protective T cell response.

j. Can effects be managed?

For the following burden / side-effects the effects can be managed, although the effects are estimated to be low <1%.

- Pain / swelling / redness, at SC injection site: painkiller and cold packages
- Bleeding / inflammation / infection / granuloma formation, at SC injection site: bandage, observation / anti-inflammatory drug – antibiotics. Granuloma formation in general can be observed for regression – ultimately in case of discomfort after 3 –6 months a surgical removal of the granuloma

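### Eligibility rules let in people already given AKS-452 who later completed a registered vaccine, although the aim is a boost after initial vaccination with a registered vaccine

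*Protocol*

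**What the plan says.** The only criterion on earlier trial products is in Protocol section 4.3: "Receipt of another investigational agent within 30 days or 5 times the product half-life (whichever is longest) prior to vaccination". On vaccination history, section 4.2 requires that "All participants have received a completed (registered) vaccine at least 3 months before inclusion in this study". It does not require the registered vaccine to have been the first or the only COVID-19 vaccine. No line in 4.2 or 4.3 mentions earlier AKS-452 or AKS-452X, another investigational COVID-19 vaccine, or participation in the sponsor's phase I/II study.

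The aim in section 9.3, like that in the Summary, concerns a booster at least 3 months "post initial vaccination, with any of the four registered vaccines".

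Section 5.4 counts "six cohorts totaling 60 participants in phase I and 52 in phase II" who were given AKS-452. Section 1.4 adds that the "phase I single-injection groups are receiving a single additional injection of non-adjuvanted AKS-452X" at 90 µg, the same non-adjuvanted product and dose as in this study. Section 12.1 states that "Phase II is currently ongoing and as part of an ongoing combined phase I/II clinical study", with last follow-up expected in February 2022.

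Cohorts are defined by the registered vaccine received. The primary result is a percentage per cohort at day 28 (section 7.1.1), and the only analysis population defined is everyone boosted (section 9.1).

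**The concern.** A washout of 30 days or 5 half-lives suits an agent whose effect ends when it is eliminated. Sections 1.2 and 1.4 describe AKS-452 as acting on existing SARS-CoV-2-specific memory B cells and as working best in a primed immune system. Memory induced by the same antigen outlasts the protein. The half-life limb is also hard to apply to AKS-452: the protocol gives no half-life, and section 12.1 says the vaccine reaches no detectable systemic level.

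Someone primed with AKS-452, and perhaps already given AKS-452X, who then completed a registered vaccine is therefore outside the population named in the aim but inside the eligibility rules. Each cohort percentage is meant to describe AKS-452X after one named registered vaccine. Subjects with earlier exposure to the same fusion antigen would mix a different question into it.

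**Working it through.** **1. Does any criterion keep such a person out?** Take someone given AKS-452 in phase I/II whose washout has passed and who completed a registered vaccine at least 3 months ago.
- Section 4.2, registered vaccine: met.
- Section 4.3, investigational agents: not triggered once the time limit has passed.
- Section 4.3, investigator's discretion: covers safety, rights and ability to comply, not antigen history.
- Section 10.2, pre-screening survey: checks the inclusion and exclusion criteria, so it carries the same gap.

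The person is eligible. By sections 7.1.1 and 9.1, the person counts by default in the cohort of the registered vaccine.

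**2. How large is the pool?** From section 5.4, 60 + 52 = 112 people were given AKS-452. The phase I single-injection cohorts are 1, 3 and 5 (section 3) with 10 subjects each, so up to 3 × 10 = 30 are also receiving AKS-452X. The pool of 112 is a ceiling: 112/600 = 18.7% of planned enrolment. The protocol does not say how many of them later had a registered vaccine or would volunteer.

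**3. The plan's own sample size** (section 4.4, Table 2: null 0.70, alternative 0.80, one-sided alpha 0.05, power 0.80).

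n = [1.645·√(0.7·0.3) + 0.842·√(0.8·0.2)]² / (0.80 − 0.70)² = 118.9, so 119 as stated. With 20% drop-out, 119/0.8 = 148.75, so 149; the protocol uses 150.

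**4. Rejection threshold at 119.** 0.70 + 1.645·√(0.21/119) = 0.7691, and 0.7691 × 119 = 91.5, so 92 or more responders. The exact binomial chance of 92 or more is 0.048 at a true 70% and 0.804 at a true 80%.

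**5. Illustration.** Assume m of the 119 are earlier AKS-452 recipients responding at rate r, and the other 119 − m respond at p. The number of responders is Bin(m, r) + Bin(119 − m, p). The values of m and r are assumptions; the protocol gives neither. The chance of 92 or more responders when p = 0.70 is:

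| m | r = 50% | r = 100% |
|---|---|---|
| 0 | 0.048 | 0.048 |
| 1 | 0.044 | 0.054 |
| 6 | 0.028 | 0.093 |
| 12 | 0.016 | 0.166 |

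When p = 0.80, power is 0.804 with none. With 12 such subjects it is 0.52 at r = 50% and 0.93 at r = 100%.

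**6. Why r can lie on either side.** Earlier priming could make a rise easier. But under section 7.1.1 a subject at or above 2.42 µg/mL at baseline responds only by at least doubling that value, which a high baseline makes harder.

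**The case against.** The criterion is a conventional washout and states nothing false. The number affected is probably small, and with one such subject in a cohort the error rate hardly moves. Past SARS-CoV-2 infection is not excluded either, and Table 1 names prior infection among the booster indications, so the protocol already accepts mixed priming. Infection may be a much larger source of it. Medical and medication history is taken at screening, and an analysis plan not shown could set such subjects apart.

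Much of this stands and keeps the point minor. It does not close the gap. The aim names the initial vaccine explicitly, which it does not do for infection history. An analysis plan can set people apart only if the exposure has been recorded, and it cannot change who is eligible.

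Four stronger readings are not supported by the documents:
- **The product profile forbids repeat exposure.** A reader might infer this from "Maximum of one booster immunization regardless of age" in Table 1. That table lists desired targets, not eligibility rules, and the same row foresees further boosters at intervals.
- **The bias favours the vaccine.** Only the assumption that all such subjects respond gives the upper figures; the range runs both ways.
- **The earlier study ran at the same centre.** The phase I/II site is not named separately, so this is an inference.
- **The safety summary is flattered by people who tolerated AKS-452 before.** Nothing in the documents shows this, and repeat exposure could equally increase reactions.

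**Conclusion.** The gap holds on the text. Sections 4.2 and 4.3 admit earlier AKS-452 and AKS-452X recipients whom the aim does not describe, by a washout rule that does not fit the mechanism the protocol sets out. It is a cheap improvement, not a flaw that threatens the trial. The pool is at most 112, and the number who would enrol is unknown and probably small. With 6 to 12 such subjects in one cohort of 119 and response between 50% and 100%, the chance of a positive test at a true 70% in the others lies between 0.016 and 0.166, against 0.048 with none. That range rests on assumed counts and rates and fixes no direction. That such subjects would count in a registered-vaccine cohort is the default under this protocol; an analysis plan not at hand could provide otherwise.

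**What to change.** Add one exclusion to section 4.3: previous receipt, at any time, of AKS-452, AKS-452X or another investigational SARS-CoV-2 vaccine, or current participation, including follow-up, in the phase I/II study. Keep the existing washout for all other investigational agents. Add the same question to the pre-screening survey in section 10.2.

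If the sponsor prefers to admit these people, the protocol should say so, record the exposure, state how they are assigned and analysed, and reconcile this with the aim.

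The cost is one line of text and the loss of a few volunteers. The sample size stays at 119 evaluable and 150 enrolled per cohort.

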#### 4.4 Sample size calculation

The study consists of a Phase II clinical study. The following stopping-rule will be applied on a cohort-by-cohort basis: for a particular cohort, any SAE or AE  $\geq 3$  (according to NCI Common Terminology Criteria for Adverse Events [CTCAE]) attributable to AKS-452X.

On the basis of the phase I/II safety assessment data conducted and a minimum project enhanced immune response rate of 80% for each cohort.

Enhanced immune response rate is defined as:

- i) Seroconversion based on a true positive based on the SP/RBD IgG ELISA assay positive/negative cutoff criteria using the quantitative cut-off value defined by the assay kit batch expressed in  $\mu\text{g/mL}$ . The positive/negative cutoff value was established as 2.42  $\mu\text{g/mL}$  from the validation analysis for the current lot of assay kits, but it should be noted that for each new lot of assay kits, Akston QC performs a re-validation of the cutoff value in order to maintain clinical agreement from lot-to-lot, and/or
- ii) Two times (2x) the baseline SP/RBD IgG at day 28 after boosting, as compared to the titer just before vaccination (day 0).

Based on the observed seroconversion rates in phase I/II and the statistical assessment for the phase II ACT-BOOSTER, a total study group of 150 subjects per cohort of registered vaccine (i.e. Pfizer [Comirnaty], Moderna [Spikevax], Janssen [Ad26.COV2.S], AstraZeneca [Vaxzevria]), totalling 600 subjects is regarded statistically significant to confirm the hypothesis. The statistical assessment providing the above stated numbers is based on the following argumentation (see Table 2 and Figure 9).

| Fixed Scenario Elements |                      |
|-------------------------|----------------------|
| Method                  | Normal approximation |
| Number of Sides         | U                    |
| Null Proportion         | 0.7                  |
| Nominal Power           | 0.8                  |
| Variance Estimate       | Null Variance        |
| Alpha                   | 0.05                 |

| Computed N Total |            |              |         |
|------------------|------------|--------------|---------|
| Index            | Proportion | Actual Power | N Total |
| 1                | 0.80       | 0.800        | 119     |
| 2                | 0.82       | 0.802        | 81      |
| 3                | 0.84       | 0.803        | 58      |
| 4                | 0.86       | 0.803        | 43      |
| 5                | 0.88       | 0.806        | 33      |
| 6                | 0.90       | 0.812        | 26      |
| 7                | 0.92       | 0.802        | 20      |
| 8                | 0.94       | 0.807        | 16      |

**Table 2:** The POWER procedure Z test for binomial proportion

[figure not shown]

**Figure 9.** The POWER procedure Z test for binomial proportion

- If we consider a realistic minimum 80% conversion rate outcome in the phase II ACT-BOOSTER study, each treatment cohort will consist of 119 subjects. Considering a drop-out rate of 20%, this relates to 150 subjects per cohort (totaling 600 subjects). The minimum 80% conversion rate is considered realistic since the one single-dose injection cohort of 90 µg and the two-dose injection of 45 µg each demonstrated a 100% conversion rate in phase I/II.

Based on the above assessment of the statistical analysis, a total of 150 subjects per registered vaccine cohort will be included for the Phase II ACT-BOOSTER study, as this relates to a realistic outcome estimate based on the phase II ACT-study seroconversion rates for a single-dose injection group of 90 µg (26 subjects) and two-dose injection group of 45 µg (26 subjects), totaling 52 participants.

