#### **7.7 . Premature termination of the study**

Termination based on safety aspects: A multidisciplinary team with study investigators ([co]PI's and dedicated research physicians) together with the sponsor will discuss safety aspects during the study procedures.

The CTCAE stopping rules for first in human studies will be leading to grade a possible SAE and how to proceed if an SAE occurs.

The termination rules are as follows: When an SAE and/or AE  $\geq$  grade 3 NCI CTCAE (attributable to AKS-452X) occurs after the s.c. injection: terminate the study for all cohorts (e.g. if an SAE occurs in cohort 1, 2, 3, or 4, terminate the entire study).

Termination based on other aspects: The study will be suspended based on urgent medical or ethical considerations as decided by the principal investigators (additional to section 8.7). In case of termination of the study, the sponsor, the institution, regulatory authorities (CCMO will be informed. Moreover, sponsor's medical monitor (or designee) may stop or suspend the trial due to safety concerns from the sponsor. Furthermore, sponsor may stop the trial due to other concerns.

Mandatory: A cohort must demonstrate a minimum of 80% seroconversion (in case a subject dropouts before day 28, he/she will be replaced with another subject. A cohort must include a

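### Sections 4.4 and 7.7 give the same safety event two different scopes: one stops a single cohort, the other ends the whole study

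*Protocol*

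**What the plan says.** Section 4.4 (Sample size calculation) opens with the safety rule: "The following stopping-rule will be applied on a cohort-by-cohort basis: for a particular cohort", the trigger being an SAE, or an AE of CTCAE grade 3 or higher, attributable to AKS-452X. It names a trigger and a unit, the single cohort, but does not spell out the action.

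Section 7.7 (Premature termination of the study) begins "The termination rules are as follows: When an SAE and/or AE" of grade 3 or higher by NCI CTCAE, again attributable to AKS-452X, and gives the consequence: "terminate the study for all cohorts (e.g. if an SAE occurs in cohort 1, 2, 3, or 4, terminate the entire study".

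Section 4.4 then sizes each cohort with a one-sided test of one proportion (null 0.70, alternative 0.80, alpha 0.05) and concludes that "each treatment cohort will consist of 119 subjects". Allowing for 20% drop-out, this becomes 150 per cohort and 600 in total. Section 7.7 also requires at least 119 subjects per cohort for the final analysis, and Section 7.5 permits replacement up to that number. Section 8.5 states that there will be no DSMB for this study.

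**The concern.** One event has two written scopes. Under Section 4.4 the rule concerns the cohort in which the event occurred. Under Section 7.7 the same event ends all four cohorts. The investigator has to act on a qualifying event at once, and the protocol does not say whether vaccination in the other three cohorts may go on.

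The study is open-label and single-centre with no DSMB, so no independent board is in place to settle the question. Section 7.7 leaves safety discussion to the investigators together with the sponsor. They would be choosing between two written rules after seeing the event, when the choice should already be fixed.

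Scope also has a statistical side. A stop during enrolment ends the replacement on which Section 7.5 relies, so it can decide whether cohorts without an event reach the 119 subjects that Section 7.7 requires.

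**Working it through.** **1. The two rules side by side**

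| | Section 4.4 | Section 7.7 |
|---|---|---|
| Trigger | SAE, or AE of CTCAE grade 3 or higher, attributable to AKS-452X | The same |
| Scope | The particular cohort | All cohorts, for an event in any one of cohorts 1 to 4 |
| Number of events | Any | Any |

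The trigger is the same, so the sections cannot be read as covering different situations. If Section 7.7 governs, no event remains for which a cohort-level rule could operate. Section 7.7 is also not obviously text left over from phase I: that study had six cohorts (Section 3), whereas Section 7.7 numbers four, matching this study's arms. No sentence gives either section precedence.

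**2. The plan's own sample size**

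Inputs from Section 4.4: p0 = 0.70, p1 = 0.80, one-sided alpha 0.05, power 0.80, null variance in the test statistic.

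n = [(z(0.95)·√(0.7 × 0.3) + z(0.80)·√(0.8 × 0.2)) / 0.10]²
= [(1.645 × 0.4583 + 0.842 × 0.4) / 0.10]² = 118.9, so 119.

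Power at 119 is 0.8003, against 0.800 in the table. The other seven rows of Table 2 reproduce as well. An exact binomial check at n = 119, with success at 92 or more responders, gives alpha 0.048 and power 0.804. For drop-out, 119 / 0.8 = 148.75, so 149; the plan uses 150. The calculation is sound for a cohort that reaches 119 evaluable subjects. It contains no term for a safety stop.

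**3. How far the two scopes differ (illustration only)**

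The protocol gives no rate for the trigger event. Assume a per-subject probability q, with independent events. Then P(at least one event) = 1 − (1 − q)^n.

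| Assumed q | Cohort of 150 | Study of 600 |
|---|---|---|
| 0.1% | 1 − 0.999^150 = 14% | 1 − 0.999^600 = 45% |
| 0.5% | 1 − 0.995^150 = 53% | 1 − 0.995^600 = 95% |
| 1% | 1 − 0.99^150 = 78% | 1 − 0.99^600 = 99.8% |

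These figures count an event at any time. AEs are recorded to day 273 (Section 8.2.1), while the primary endpoint is read at day 28 (Section 7.1.1). They are chances that a rule is triggered, not losses of power.

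**The case against.** **Section 4.4 does not require the other cohorts to continue.** This is true. It states a trigger and a unit but no action. Stopping all four cohorts also stops the affected one, and Section 7.7 separately lets the sponsor stop the trial for safety or other concerns. A reader might infer that whichever action is taken breaches one of the sections. That goes too far: the clear conflict arises when the other three cohorts continue, which Section 4.4 leaves open and Section 7.7 forbids. The conflict still needs resolving, because a rule declared to work by cohort has no purpose if every trigger ends the study. The sponsor's discretion to stop does not say which predefined rule applies.

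**The 80% power is correct.** This also stands. A reader might infer from the conflicting rules that the stated power holds under neither. The documents do not support that. The figure reproduces for 119 evaluable subjects, and both rules leave it untouched if no trigger occurs. If every stop were counted as a failed cohort, an assumed q of 0.1% would turn 0.80 into about 0.69 under the cohort scope and 0.44 under the study scope. But the protocol does not say that a stopped cohort goes unanalysed. Section 7.4 asks boosted drop-outs to complete follow-up, and Section 7.6 still seeks titers from withdrawn subjects. Events after a cohort's day 28 samples cost no primary data. Table 2 itself shows 80% power with 58 subjects at a true rate of 0.84 and with 26 at 0.90.

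**The event rates are assumed.** They are. Section 5.4 reports no attributable SAE among 60 + 52 = 112 earlier participants, which would give a one-sided 95% upper bound of 1 − 0.05^(1/112) = 2.6% for SAEs. That is not a bound on the trigger, because no count of grade 3 or higher AEs is given and the earlier data come mainly from the adjuvanted product.

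**Conclusion.** The contradiction stands and rests on wording alone, with no assumed figures: the same attributable event has a cohort-level scope in Section 4.4 and a study-wide scope in Section 7.7, with no order of precedence and no DSMB. It bears on subject safety and is cheap to repair, so it should be settled before any dosing that depends on it.

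The stop probabilities only illustrate that the choice of scope is consequential. They depend on the assumed rates, on independence between subjects and on counting events at any time. They do not show the sample size to be wrong. What can be said is that the 80% applies to a cohort whose day 28 data are completed without a safety stop.

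**What to change.** Reconcile Sections 4.4 and 7.7. The sponsor and the ethics committee should choose one scope, and it should appear in identical words in both places, including what happens to cohorts in which no event has occurred. Which scope is appropriate is a clinical and ethical decision, and none is proposed here.

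Optionally, add one sentence to Section 4.4 saying that the 119 per cohort and the 80% power are conditional on no safety stop before that cohort's day 28 data are complete. The figures themselves need no change.

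The cost is wording in two sections. Because the text concerns subject safety, it would probably count as a substantial amendment under Section 11.3. No additional subjects, visits or analyses are needed.
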